### **7.1 Data Sources**

Figure 1 below illustrates the data sources used in the LeAf Trauma study. The patient and expert interviews listed there are described in detail in Ethical Application 1 – Qualitative Study Arm. The importance of these interviews for the other study arms is evident from the figure: Qualitative data play a significant role, particularly for the prospective cohort study and also for the analysis of secondary data from WIdO. Below, the three other data sources, their methodologies, and their interrelations are described in detail.

Figure 1: Data Sources

#### **7.1.1 Preliminary to the Prospective Cohort Study**

The sections of the questionnaire that emerged from the qualitative group interviews (described in Ethical Application 1 – Qualitative Study Arm) will be evaluated in a pretest for clarity and usability and may be adjusted before being used in patient care (Version 1.0). The pretest will be conducted with patients who have completed their treatment and participated in the interviews. The follow-up assessment processes will be developed based on the results of patient interviews, literature research, and discussions with stakeholders from previously conducted follow-up studies on severely and critically injured patients, taking into account data protection and technical conditions (see Ethical Application 1 – Qualitative Study Arm).

#### **7.1.2 Prospective Cohort Study**

All participating study clinics will receive at least two training sessions explaining the study and follow-up procedures in detail. The recruitment, administration, tracking, and follow-up throughout the entire study will be conducted by the respective study clinic, which will

receive a tiered compensation of up to €660.00 per patient based on the number of successfully documented follow-ups in the web-based study database. Documentation of all assessments will be conducted exclusively in a pseudonymized manner in the web-based study database. The assignment list will be managed by the respective study clinic for the included patients.

After obtaining informed consent for study participation, baseline data will be collected before discharge (clinical data, profession, situation before the accident – exact contents are based on the results of patient and expert interviews as described in Ethical Application 1, Qualitative Study Arm; further information can be found in the section on Data Collection).

## **Follow-Up Assessments**

Follow-up assessments will be conducted 6, 12, and 18 months after the trauma, including the PREM and PROM developed in the project (see Figure 2). The optimal follow-up assessment processes will be developed based on the results of patient interviews, literature research, and discussions with stakeholders from previously conducted follow-up studies on severely and critically injured patients, while considering data protection and technical conditions. For the follow-up, patients will be surveyed either by mail or by phone from the respective study clinics. They will not be summoned by the study clinics. In an initial work package of the overall project, a patient group-specific assessment methodology for follow-up will be developed. If postal surveys prove to be the best method of inquiry for this patient group, responses will be returned to the treating study clinic. Other partners will not have knowledge of the patients' identities.

Figure 2: Flowchart of the Prospective Cohort Study LeAf Trauma

\*FU = Follow Up, GCS = Glasgow Coma Scale, MAIS = Maximum Abbreviated Injury Scale

## **Interim Evaluation**

An interim evaluation of the study results will take place (after the 6-month and 12-month follow-ups), where the results (content-wise) from the follow-ups will be analyzed and compared with the findings from the patient and expert interviews (see Ethics Application 1 – Qualitative Study Component). These results will be supplemented with insights from the routine data analysis (October 2022 to June 2023) and interdisciplinary evaluations of the same, involving intersectoral experts. This may lead to an expansion of the PREMs and PROMs used in the questionnaire (Development of Questionnaire Version 1.1), which will then be employed in the 18-month follow-up. The goal of the interim evaluation is to determine whether further aspects relevant to the recovery process, health-related quality of life, and the regaining of work capacity have emerged in discussions with patients that were not included in the previous questionnaire and can be added as "free text." This may result in the need to adjust the PROMs and PREMs. A revised version of the PROMs and PREMs is expected to be used in the 18-month follow-up.

Figure 3: Flow of the Prospective Cohort Study

After the follow-up period, the contributors from the study clinics will share their experiences regarding the data collection, patient feedback, and their personal assessment of the data collection processes through an online survey.

The evaluation of the prospective study will commence with the preparation of the analysis algorithms in the 4th project quarter (2023). Interim results will contribute to the temporal and content characterization of patient pathways and the care reality of severely and critically injured GKV patients.

### **7.1.3 WIdO Data**

The secondary data from WIdO will be utilized to characterize the temporal and content-related post-hospital treatment pathways of severely and critically injured patients until the regaining of work capacity over three years. To identify severely and critically injured patients, their subsequent diseases and treatments, as well as their predictors in routine data, definitions must first be developed based on medical knowledge that can be operationalized in GKV routine data. These are currently being developed and will then be submitted to WIdO. Furthermore, unfavorable disease courses for trauma-specific subgroups will be characterized. In medical expert groups, possible outcomes in defined post-hospital periods will be marked as unfavorable courses, e.g., readmissions, infections, non-unions, reoperations. The regaining of work capacity as a primary outcome, along with unfavorable courses, will be analyzed for previously identified relevant subgroups concerning possible predictors.

Only WIdO will conduct the analysis of this cohort, and the other consortium partners will receive only anonymized aggregated data of the defined cohort. These data will not be linked with other project data and cannot be traced back to a specific patient. WIdO will utilize nationwide AOK data from the years 2015 to 2020 for this purpose.

### **7.1.4 TraumaRegister DGU**

The data from the TraumaRegister DGU from the years 2015 to 2017 will be used for a more in-depth representation of the cohort, for example regarding injuries and representativeness. Many clinical data of severely and critically injured patients are documented in the TraumaRegister DGU. The application includes the standard form for collecting patients in the TraumaRegister DGU, which provides an overview of the data to be collected in the TraumaRegister DGU. The data from the TraumaRegister DGU can only be analyzed through a formal request. This procedure is regulated by the application and review process according to publication guidelines (as described here: <https://www.traumaregister-dgu.de/forschung>). The data will then only be incorporated into the project in anonymized aggregated form.

### **7.1.5 Data Collection for the Prospective Cohort Study (Baseline and Follow-Up)**

Patients will be surveyed a total of four times in the prospective arm of the study (baseline, 6, 12, and 18 months follow-up). At the time of discharge from the study clinic, a baseline survey will be conducted, followed by the follow-up collection of Patient-Reported Outcomes (PROs) regarding health-related quality of life (hrQoL) and work ability (AF), as well as an evaluation of the treatment pathway experienced by the patient (Patient-Reported Experiences (PREs)). The collection of patient data will be conducted via a questionnaire. The questionnaire will consist of several modules. Validated questionnaires will be used whenever possible. The measurement instruments listed under "Assessment of Influences on Work Ability after Trauma (PROM)" and "Patient-Reported Experience Measures (PREMs)" will be selected based on the patient and expert interviews and supplemented with independently constructed questions. The completion of the questionnaire should not take longer than 30

minutes. Before the start of patient recruitment, the questionnaire will undergo a pretest and will be revised as necessary.

- **TraumaRegister DGU Standard Form** (only during baseline survey, see attached documents)
- **Assessment of Quality of Life after Trauma (PROMs)**
  - POLO Chart  
- **Assessment of Influences on Work Ability after Trauma**
  - Health-related factors (physical and psychological)
  - Sociodemographic factors
  - Individual factors and personality structure
  - Rehabilitation-related factors
  - Workplace-related factors
  - Injury characteristics and information regarding the hospital stay
- **Patient-Reported Experiences (PREMs)**
  - Treatment and care in the acute clinic
  - Assessment of medical interfaces in the patient pathway
  - Description of organizational hurdles with authorities and institutions

It is expected that additional characteristics of patient experience in the treatment pathway will be highlighted in the patient and expert interviews; these will be considered in the construction of the questionnaire.

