### **5.1 Research Questions of the Overall Project**

The following research questions have been formulated for the overall project:

- i. What is the current reality for severely injured patients regarding their return to the workforce?

- ii. Who will be able to return to work, and when?
- iii. What influencing factors (e.g., patient, occupation, accident circumstances, injury patterns, and therapy across different sectors) exist concerning the restoration of work ability, and can these be influenced?
- iv. How does health-related quality of life (hrQoL) develop over time following a severe injury until work ability is restored?
- v. What characterizes favorable and unfavorable patient pathways and trajectories?

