## **7. Methodology and Implementation**

To address the research questions, the project pursues a quantitative approach consisting of two cohorts of severely and critically injured patients, complemented by qualitative methods. Cohort 1 is a multicenter, non-interventional, prospective study focusing on clinical data, patient-reported experiences (PREs), and patient-reported outcomes (PROs). In Cohort 2, the focus is on retrospective analysis. For this, GKV routine data from the Scientific Institute of the AOK (WIdO) will be analyzed regarding patient pathways up to their reintegration into the workforce.

Qualitative methods are described in the ethical application 1 – qualitative study arm; these serve as the basis for parts of the questionnaire used in the multicenter, non-interventional, prospective cohort study. This questionnaire will be supplemented in the baseline survey by the DGU Trauma Register standard questionnaire (attached) and in the follow-up by existing instruments for surveying severely and critically injured patients identified through literature research.

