## 7.2 Statistical Analysis

- **Description of Progress:** All patients; description of the regaining of work ability (AF) and health-related quality of life over time (3 follow-up points; descriptive statistics).
- **Predictors for AF:** AF up to 18 months after trauma as a yes/no criterion; univariate and multivariate analysis (logistic regression) of possible predictors; classification of predictors into the categories: patient, profession, pre-hospital, clinic, post-acute therapy, presence of psychological problems (from QoL assessment at follow-up time).
- **Predictors for Time until AF:** Only patients with regaining AF: Time until AF as a dependent variable, Kaplan-Meier curves for description, Cox regression for multivariate analysis, predictors as above.
- **Health-related Quality of Life and PREMs:** Description at the 3 follow-up points, correlation with AF as subgroup comparisons at each measurement time.

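### The protocol plans hrQoL only at 6, 12 and 18 months, so patients who regain work ability before 6 months have no planned hrQoL value before that event

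*Protocol*

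**What the plan says.** Research question iv (section 5.1) reads: "How does health-related quality of life (hrQoL) develop over time following a severe injury until work ability is restored".

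On data collection:
- Section 7.1.5: "Patients will be surveyed a total of four times in the prospective arm of the study (baseline, 6, 12, and 18 months follow-up". The baseline survey takes place at discharge, "followed by the follow-up collection of Patient-Reported Outcomes (PROs) regarding health-related quality of life (hrQoL) and work ability (AF".
- Section 7: the register form supplements the questionnaire at baseline. It is supplemented "in the follow-up by existing instruments for surveying severely and critically injured patients identified through literature research".
- Follow-Up Assessments: "Follow-up assessments will be conducted 6, 12, and 18 months after the trauma, including the PREM and PROM developed in the project".
- Section 7.1.2: baseline covers clinical data, profession and the "situation before the accident – exact contents are based on the results of patient and expert interviews".
- Section 7.1.5, module list: the register form is marked as baseline only. The POLO Chart, the named quality-of-life instrument, has no time mark.

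On analysis, section 7.2 counts three follow-up points for the description of hrQoL over time. For hrQoL and PREMs it plans "Description at the 3 follow-up points, correlation with AF as subgroup comparisons at each measurement time".

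**The concern.** Question iv is about a course that starts at the injury and ends at an event, the return of work ability. To describe it, a patient needs at least one hrQoL value before that event. If the first value is taken at 6 months, a patient who is fit for work at 4 months contributes only values from after the event. For all patients, the first 6 months of recovery are unobserved.

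This matters because hrQoL is one of the two patient-relevant endpoints named in section 2.1 and the subject of Hypothesis 2. Early returners are also the group most likely to show what a favourable pathway looks like (question v). A statistical analysis plan cannot repair the gap, since a value not collected at discharge cannot be recovered. The interim questionnaire revision affects only the 18-month survey.

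**Working it through.** **Step 1. Where is hrQoL planned?** Section 7, the Follow-Up Assessments text and section 7.1.5 all place the outcome instruments in the follow-up. Section 7.2 counts three hrQoL time points, while section 7.1.5 counts four surveys. The survey without a planned hrQoL value is therefore the one at discharge. Nothing expressly excludes such a value, but none is planned, and the analysis as written would not use one.

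**Step 2. hrQoL values before return, by time of return.**
- Before 6 months: 0
- 6 to 12 months: 1
- 12 to 18 months: 2
- Not returned by 18 months: 3 values, no event

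**Step 3. How many return before 6 months?** The protocol gives no figure, so this is an assumption with a range. Inputs:
- Cohort of 1000 evaluable patients (section 6.3.1).
- About 30% not back at work (section 6.3.1), hence 70% returned. No time point is stated; 18 months is assumed. The same 30% reproduces the protocol's predictor count: 0.30 × 1000 / 10 = 30.
- About 30% able to work two years after the accident (section 4, pilot study).

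Let a share p have returned by month T, with Weibull shape k (k = 1 is a constant hazard; k = 1.5 is a rising hazard, which allows for few returns in the first weeks). The share returned by month t is

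F(t) = 1 − (1 − p)^((t/T)^k)

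For t = 6:
- p = 0.70, T = 18, k = 1: 1 − 0.30^(1/3) = 33.1%
- p = 0.70, T = 18, k = 1.5: 1 − 0.30^(0.192) = 20.7%
- p = 0.30, T = 24, k = 1: 1 − 0.70^(0.25) = 8.5%
- p = 0.30, T = 24, k = 1.5: 1 − 0.70^(0.125) = 4.4%

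Per 1000 patients (rounded):

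| Scenario | <6 mo | 6–12 mo | 12–18 mo | Not by 18 mo |
|---|---|---|---|---|
| 70% by 18 mo, constant | 331 | 221 | 148 | 300 |
| 70% by 18 mo, rising | 207 | 274 | 219 | 300 |
| 30% by 24 mo, constant | 85 | 78 | 71 | 765 |
| 30% by 24 mo, rising | 44 | 75 | 88 | 793 |

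**Step 4. What a discharge value changes**, among those who return by 18 months:

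| Scenario | No value before return, as planned | Two or more, as planned | Two or more, with discharge value |
|---|---|---|---|
| 70% by 18 mo, constant | 47% | 21% | 53% |
| 70% by 18 mo, rising | 30% | 31% | 70% |
| 30% by 24 mo, constant | 36% | 30% | 64% |
| 30% by 24 mo, rising | 21% | 43% | 79% |

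First row: 331/700 = 47%, 148/700 = 21%, (221 + 148)/700 = 53%. With a discharge value, everyone who returns after discharge has at least one earlier value.

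The 4–33% range is not a bound. Section 4 also cites a Dutch study with 58.5% in full-time and a further 21.5% in part-time work at 15 months. Taking the sum of 80% as returned by 15 months gives 33% (rising) to 48% (constant) before 6 months.

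**The case against.** The strongest reply is that the protocol never says hrQoL is left out at discharge. Baseline covers the situation before the accident, its contents are to follow from the interviews, section 7.1.5 is headed as covering both baseline and follow-up, and the POLO Chart has no time mark there. The flowcharts and the questionnaire were not available for this check. This stands: a discharge or recalled pre-injury value is unplanned, not excluded. A reader might infer that it is missing for every patient; the text does not establish that.

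A reader might also infer that question iv cannot be answered at all, or that there are no hrQoL data on early returners. Neither holds. Early returners are still surveyed at 6, 12 and 18 months and lack only a value before return. Later returners have one or two such values.

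A third tempting reading is that the missing pre-injury value alone defeats the aims. Question iv starts at the injury and needs no pre-injury value. Section 7.2 provides for patient, profession and pre-hospital predictors of work ability, so some adjustment for prior status is possible there. It plans no regression for hrQoL that a pre-injury covariate could enter.

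Finally, the fix is only partial. One discharge value leaves the interval from discharge to 6 months unobserved. The protocol does not show that the instrument suits inpatients or recalled ratings, and recall may be poor after traumatic brain injury, a subgroup named in section 6.3.1. These limits are real, but they do not remove the mismatch between question iv and section 7.2.

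**Conclusion.** The point holds in limited form. As written, the protocol plans and analyses hrQoL at 6, 12 and 18 months only, although a survey already takes place at discharge. Question iv therefore has no pre-return value for patients who regain work ability before 6 months, and an incomplete course for those who regain it later.

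The size depends on an unknown return curve. Under the two main calibrations the affected group is about 4% to 33% of the cohort, or 21% to 47% of those who return by 18 months. A reader might take one third of the cohort as the expected figure. That is the top of this range and rests on attaching an undated 30% to 18 months with a hazard constant from the day of injury. The pilot-study figure in section 4 gives about 8.5% by the same method.

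This is an inexpensive improvement worth making before recruitment. It is not a flaw that invalidates the study.

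**What to change.** 1. In section 7.1.5, state that the hrQoL part of the chosen instrument is included in the existing discharge survey, asked for current status. Add a short recalled rating of the pre-injury state if it fits within the 30-minute cap.
2. In section 7.2, describe hrQoL over all four time points. If the recalled pre-injury rating is collected, use it as a reference value and acknowledge recall bias. Compulsory adjustment for it in every analysis is not needed.
3. If a discharge value is not wanted, restrict question iv to the course from 6 months on, and say that the course before return is not observed for patients who regain work ability earlier.

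Cost: a few minutes in a survey that already takes place, with no extra visit. The minutes are an estimate, since the protocol gives no instrument length; the pretest already planned before recruitment can check this and whether the items work at discharge. The recalled rating brings some recall bias, and the interval from discharge to 6 months stays unobserved.

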## 7.2 Statistical Analysis

- **Description of Progress:** All patients; description of the regaining of work ability (AF) and health-related quality of life over time (3 follow-up points; descriptive statistics).
- **Predictors for AF:** AF up to 18 months after trauma as a yes/no criterion; univariate and multivariate analysis (logistic regression) of possible predictors; classification of predictors into the categories: patient, profession, pre-hospital, clinic, post-acute therapy, presence of psychological problems (from QoL assessment at follow-up time).
- **Predictors for Time until AF:** Only patients with regaining AF: Time until AF as a dependent variable, Kaplan-Meier curves for description, Cox regression for multivariate analysis, predictors as above.
- **Health-related Quality of Life and PREMs:** Description at the 3 follow-up points, correlation with AF as subgroup comparisons at each measurement time.

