**Tab. 3: Inclusion and Exclusion Criteria**

| Study Part                      | Inclusion Criteria                                                                                                                                             | Exclusion Criteria                                                                                                                                                                                                                                                                                                                                                                                            |
|---------------------------------|----------------------------------------------------------------------------------------------------------------------------------------------------------------|---------------------------------------------------------------------------------------------------------------------------------------------------------------------------------------------------------------------------------------------------------------------------------------------------------------------------------------------------------------------------------------------------------------|
| Prospective Cohort Study | 
 
Severely injured patients of working age (18-55 years) with an injury severity of MAIS* <math>\geq 3</math>;
 
 | 
 
Patients who are not communicative after the acute phase (inclusion point) (Glasgow Outcome Score <math>< 3</math>)
 
Insufficient German language skills (at least B1 language level according to the European Reference Framework)
 
Patients after a suicide attempt
 
Patients without a permanent residence or residing abroad
 
 |
| DGU Trauma Register      | 
 
Admission of a patient via the emergency room with subsequent intensive therapy
 
                              | 
 
Patients with less severe injuries
 
                                                                                                                                                                                                                                                                                                                          |

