| Study Part          | Inclusion Criteria                                                                                                                                                                                                                                                                                                                                                 | Exclusion Criteria                                                                                                                                                                                              |
|----------------------------|---------------------------------------------------------------------------------------------------------------------------------------------------------------------------------------------------------------------------------------------------------------------------------------------------------------------------------------------------------------------------|------------------------------------------------------------------------------------------------------------------------------------------------------------------------------------------------------------------------|
|                            | 
 
• All patients documented in the TR with a MAIS* <math>\geq 3</math>,
 
• Acute stay survived
 
• Age 18-55 years
 
• Accident date 2015-2017
 
                                                                                                                                                      | 
 
• Patients after a suicide attempt
 
• Patients who are not communicative after the acute phase (inclusion point) (Glasgow Outcome Score <math>< 8</math>)
 
 |
| WIdO Secondary Data | 
 
• Insured individuals of working age (18-55 years)
 
• Severe acute hospital-treated injury survived between 2015 and 2017 and continuously insured during the observation period. The defined severe injury must correspond to a MAIS* of at least 3 (MAIS <math>\geq 3</math>) or an ISS* <math>\geq 9</math>.
 
 |                                                                                                                                                                                                                        |

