## **6.3 Sample Size Calculation**

### **6.3.1 Sample Size Calculation for Prospective Cohort Study**

As severe injuries can occur in different body regions, the present cohort is considered heterogeneous. Therefore, the cohort must be large enough to allow for analyses of patient- and injury-specific subgroups (for example, traumatic brain injury), as well as the examination of socioeconomic and psychosocial factors. With a total of  $n=1000$  evaluable cases (with complete follow-up), prevalences of 10% can be reported with an accuracy of  $\pm 2\%$  (95% confidence interval), prevalences of 20% with  $\pm 2.5\%$ , and prevalences of 50% with  $\pm 3\%$ . In subgroups of 300 cases, there is still an accuracy of  $\pm 3.5/4.5/5.5\%$  for the aforementioned prevalences.

For the multivariate analyses of risk factors, a number of 5-10 patients per factor with an “event” (in this case, work ability) should be available. If approximately 30% of patients have not resumed work, about 30 predictors could be investigated across the entire cohort, which seems sufficient.

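### Regaining work ability is described and sized in the whole cohort with no condition on work before the injury, so pre-injury status can appear as failed recovery

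*Protocol*

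**What the plan says.** Eligibility for the prospective cohort (Tab. 3) is "Severely injured patients of working age (18-55 years) with an injury severity of MAIS" of at least 3. The exclusions concern communication, language, suicide attempt and residence. None concerns employment or work ability before the accident, and working age here is an age band.

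Section 7.2 then sets out three AF analyses:
- The description covers "All patients; description of the regaining of work ability (AF) and health-related quality of life over time".
- The predictor model takes "AF up to 18 months after trauma as a yes/no criterion; univariate and multivariate analysis (logistic regression) of possible predictors" and names no population.
- The time analysis is limited: "Only patients with regaining AF: Time until AF as a dependent variable".

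Section 6.3.1 sizes the multivariate predictor analysis on an assumed 30% who have not gone back to work, and concludes that "about 30 predictors could be investigated across the entire cohort, which seems sufficient".

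AF is not defined. The research questions (Section 5.1) and the opening of Section 7 speak of return to, or reintegration into, the workforce. Section 4 treats being fit for work but without a job as a state of its own. Pre-injury information will be available: Section 7.1.2 says that "baseline data will be collected before discharge (clinical data, profession, situation before the accident" is recorded.

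**The concern.** An analysis of regaining something needs a set of people who had it to lose. The protocol names the whole cohort instead, both for the description and for the sizing of the predictor models.

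If AF means resumed work, a patient without work before the accident has none to resume and can only be a non-regainer. If AF means capacity, the same holds for a patient already unable to work before the accident. Under either meaning, pre-injury status is mixed into the outcome.

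The study aims to find modifiable determinants and to turn them into care recommendations (Section 5). Correlates of prior non-employment, such as education or earlier illness, could then appear as determinants of failed recovery and be read as shortcomings of care.

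**Working it through.** **Inputs from the protocol:** 1000 evaluable patients; 30% not resuming work; 5-10 events per factor (all Section 6.3.1).

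**Assumed:** q, the share of the cohort not working before the injury. The protocol gives no figure; 5-25% is used as an illustrative range.

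**The plan's own figure.** 1000 × 0.30 = 300 events; 300/10 = 30 predictors (300/5 = 60). The stated figure of about 30 reproduces. It uses all 1000 patients, so nobody is set aside for pre-injury status.

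**Reading A: 30% is the non-return rate among patients working before the injury, AF means resumed work, and all others count as non-regainers.**
- Observed non-return = q + (1 − q) × 0.30
- Share of non-regainers due to pre-injury status = q / [q + (1 − q) × 0.30]
- Events in the at-risk set = 1000 × (1 − q) × 0.30
- 95% half-width at 30% = 1.96 × √(0.21/n), with n = 1000 × (1 − q)

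| q | n at risk | Observed non-return | Share pre-injury | Events at risk | Predictors at 10 per factor | Events per factor with 30 predictors | Half-width |
|---|---|---|---|---|---|---|---|
| 5% | 950 | 33.5% | 15% | 285 | 28 | 9.5 | 2.91% |
| 10% | 900 | 37.0% | 27% | 270 | 27 | 9.0 | 2.99% |
| 15% | 850 | 40.5% | 37% | 255 | 25 | 8.5 | 3.08% |
| 20% | 800 | 44.0% | 45% | 240 | 24 | 8.0 | 3.18% |
| 25% | 750 | 47.5% | 53% | 225 | 22 | 7.5 | 3.28% |

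For the full 1000 the half-width is 1.96 × √(0.21/1000) = 2.84%.

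**Reading B: the 30% already includes patients not working before.** They then make up q/0.30 of the 300 non-regainers: 17% at q = 5% and 83% at q = 25%. The events among those at risk are 1000 × (0.30 − q), which is 250 at 5%, 150 at 15% and 50 at 25%. With 30 predictors that is 8.3, 5.0 and 1.7 per factor. The protocol does not say which reading its 30% follows.

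**Which analyses are touched.** The description and the logistic model are. The time-to-AF analysis takes only patients who regain AF, so a patient who can only be a non-regainer never enters it.

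**The case against.** The strongest reply is that no sentence codes a patient without prior work as AF = no. The endpoint is named work ability, it is patient-reported, and Section 4 separates ability from employment. An unemployed person or a homemaker who was fit for work could lose and regain ability and be coded yes. The phrase about not resuming work is a planning assumption, and the sentence before it names the event as work ability. The words on all patients open only the descriptive bullet, which also covers quality of life, where the whole cohort is right. Prior status is recorded, profession is a predictor category, and an at-risk set could be defined in an SAP that is not shown.

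Much of this stands. A reader might infer that the protocol analyses non-employment as failure and that non-return will be overstated. The text does not support that, because AF is undefined and the direction and size of any bias depend on the definition. Nor does it support a claim that the time-to-AF model is distorted in this way, or that the planned events are too few. Under reading A, 30 predictors stay within the stated rule. Under reading B they would fall below 5 per factor only if q exceeded 15%, and the protocol fixes neither the reading nor the share.

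Two parts of the reply fail. First, the protocol does choose a population: all patients in Section 7.2 for the description, and the entire cohort in Section 6.3.1 for the predictor models. It restricts the set where it wants to, as in the time analysis, so this is not merely a matter left open for the SAP. Second, entering profession as a predictor, even with a level for not employed, does not remove patients who cannot have the outcome.

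**Conclusion.** The point holds in a limited form. Eligibility has no condition on work before the injury, and the AF description and the planned predictor analysis use the whole cohort. Pre-injury status can therefore appear as failed recovery in the description and the logistic model. It does so for everyone not working before if AF means resumed work, and for those unable to work before if AF means capacity.

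The size is not fixed by the protocol. With q assumed at 5-25%, 30% true non-return and AF read as resumed work, observed non-return is 33.5-47.5%, and 15-53% of the non-regainers reflect status before the accident. No figure in Section 6.3.1 is arithmetically wrong on this account. The change is worth making because the possible bias is large relative to the cost of removing it.

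For the WIdO arm, Tab. 3 likewise starts from "Insured individuals of working age (18-55 years" and sets no employment condition, although regaining work capacity is its primary outcome. Section 7.1.3 says its definitions are still being developed, so this is a matter to settle there and not an established error.

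**What to change.** 1. In Section 7.2, state whether AF means work ability or resumed work, and use one term throughout.
2. Restrict the AF description and the logistic model to patients who were working, self-employed or in training before the injury or, if AF means capacity, able to work before it. Use the baseline item on profession and situation before the accident.
3. Report the work status of the other patients separately. Keep all patients for quality of life and PREMs.
4. In Section 6.3.1, say which population the 30% refers to and restate the event count for the at-risk set. Under reading A this is about 225-285 events, or 22-28 predictors at 10 per factor.
5. Consider the same at-risk rule when the WIdO definitions are set.

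In the cohort this needs wording only, with no new data collection. The price is a smaller AF analysis set: the half-width at 30% goes from 2.84% with all 1000 patients to 2.91-3.28% over the assumed range.
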